## Abstract

**Background:** Despite extensive research in the field of psychotherapies, few studies have compared the primary psychotherapies of naturalistic design, which represents real-life situations.

**Objective:** The objectives of this study were to evaluate three modalities of evidence-based psychotherapy for clinical, psychosocial, and biological outcomes and to identify the mediators and confounders of this process. Our primary hypothesis is that all psychotherapies will improve clinical and psychosocial outcomes and will increase BDNF levels.

**Methods:**
*Design:* longitudinal, naturalistic. *Participants:* One hundred twenty-six patients who underwent one of three evidence-based modalities of individual psychotherapy [psychodynamic psychotherapy (PDT), interpersonal psychotherapy (IPT), and cognitive–behavioral psychotherapy (CBT)] were included. *Measure:* Primary outcomes are divided into three domains of variables: clinical (general psychiatric symptoms), biological (serum BDNF levels), and psychosocial (resilience, quality of life, coping strategies, social support, and quality of life-adjusted years of life). Confounding/mediator variables included clinical (personality traits, type of psychotherapy, number of sessions, concomitant use of pharmacological treatment, history of previous psychotherapeutic treatment, medical and psychiatric comorbidities, and psychiatric diagnosis), psychosocial (psychosocial stressors, therapeutic alliance, and defense mechanism style), and other (religiosity) factors. *Procedure:* The follow-up period will be baseline and 6 months and 1 year after entering the study. The study will include 42 controls for biological variables only. Sample size calculation considered a significance level of 5% and a power of 80% to detect a difference of 0.22 with a standard deviation of 0.43, assuming losses of 20–30% of patients. The comparison between the modalities of psychotherapy will be by generalized estimating equations (GEE) model, the analysis of mediators by the Hayes method, and confounders by multivariate logistic regression.

**Discussion:** The findings of this study are intended to demonstrate the outcomes of evidence-based psychotherapies for clinical, psychosocial, and biological parameters and to understand the mediators and confounders of this process in a real-life setting for patients with severe mental illness, thus contributing to the establishment of evidence-based public health policies in the field of psychological interventions.

## Introduction

Psychotherapies are effective interventions for most mental disorders (1–4). A systematic review of 61 meta-analyses (852 clinical trials comprising a total of 137,126 participants) examined the effect of pharmacotherapy and psychotherapy for major psychiatric disorders. This review revealed that the effect sizes of psychotherapies tended to be larger [0.58 (95% CI, 0.40–0.76)] than those of pharmacotherapy [0.40 (95% CI, 0.28–0.52)]. This investigation concluded that more support from public funding agencies is necessary for studies of psychotherapy (4).

Comparisons between different types of psychotherapy have long been a source of controversy (5), even with subsequent reproductions of meta-analyses (6, 7). This situation persists because of the dodo bird effect, i.e., that different techniques present similar effect size outcomes. The issue becomes more complex given that most studies do not have sufficient power to detect differences between psychotherapies. Furthermore, meta-analyses are composed of clinical trials with a considerable risk of bias (8).

Although there have been many randomized clinical trials (RCTs) evaluating the outcomes of psychotherapies, this is the first protocol of a study to evaluate main available evidence-based psychotherapies using a naturalistic longitudinal design and including patients referred from primary and secondary centers with complex and severe disorders. This design has the advantage of evaluating clinical outcomes in a real-world situation. Clinical trials, on the other hand, have the standardization of interventions, but can suffer from a lack of rigorous control related to the criteria for inclusion of patients; also, longitudinal studies have a level of evidence lower than that of randomized clinical trials and meta-analyses (9). To our knowledge, this is the first study with this design, because a Swedish naturalistic study by Werbert et al. compared three psychotherapies but used public health system records. Of the 1,498 patients, only 180 remained in the study, and the records were obtained mostly online. The study showed that there was no significant effect of the type of therapy, duration, or effect of the therapist, despite the limitations.

Reviewing the longitudinal studies in psychoanalytical psychotherapy published on PubMed, PsychInfo, and Embase databases within the last 5 years, we found seven studies (10–16), all of which were European. These studies were conducted mostly on patients with personality disorder, anxiety disorders, and depressive disorders. To the best of our knowledge, no published studies have followed up patients who underwent different kinds of psychotherapy.

The question of how to evaluate outcomes in psychotherapy is quite complicated and has been the subject of numerous studies (17). The most commonly used outcome measures in recent studies have included general psychiatric symptoms (10, 14), anxiety and depressive symptoms (13), coping and defense mechanisms (12), quality of life (16), and quality of life-adjusted years of life [Short-Form Six-Dimension (SF-6D)] (10).

Psychotherapies can function by environmental epigenetic mechanisms, altering gene expression through methylation of the DNA of the serotonin transporter gene (5HTT) and altering imaging exams. However, this subject has been rarely studied (18). The search for biological markers of mental disorders has advanced in recent years, and this work has revealed neurotrophins. These neurotrophins, particularly brain-derived neurotrophic factor (BDNF), appear to be involved in the pathophysiological basis of many neurodegenerative and psychiatric disorders (19). BDNF is a neurotrophin distributed largely by the central nervous system that is involved in neuron growth, development, and plasticity (20, 21). It is associated with both mental disorders and physiological states such as sleep and alterations after interventions like electroconvulsive therapy (ECT) and antidepressants (19, 22).

Changes in BDNF have already been investigated in different psychotherapies (23) in clinical (24–26) and experimental contexts (27, 28), with contradictory results.

Patients with borderline personality disorder who underwent behavioral dialectical psychotherapy had a change of methylation of the BDNF gene at the end of the treatment that was associated with change scores in depression, hopelessness, and impulsivity (23). Patients with panic disorder who underwent cognitive–behavioral psychotherapy (CBT) and had a poor response had significantly lower serum BDNF than patients with a good response (29).

Despite the extensive literature of comparative studies of psychotherapies, there are still issues related to the effects of moderators and mediators in the psychotherapeutic process, especially considering a view of protective factors, biological factors, and outcomes that encompass factors of positive psychiatry such as quality of life and resilience. In addition, further studies are needed in naturalistic and severe patient contexts that assess psychotherapy in practice, seeking external validity.

## Aims

Our primary aim is to evaluate the outcomes associated with different forms of individual psychotherapy [psychodynamic psychotherapy (PDT), interpersonal psychotherapy (IPT), and CBT] in a public outpatient clinic for mental disorders. Our primary outcomes are divided into three domains of variables: clinical (general psychiatric symptoms), biological (serum BDNF levels), and psychosocial (resilience, quality of life, social support, and quality of life-adjusted years of life).

Our secondary aim is to evaluate potential confounders/mediators/moderators for the main outcomes: personality traits, type of psychotherapy, number of sessions, the therapist’s duration of training, concomitant use of pharmacological treatment, history of previous psychotherapeutic treatment, medical and psychiatric comorbidities, psychiatric diagnosis, therapeutic alliance, and defense mechanisms.

Our main hypothesis is that all three modalities of therapy will produce reduction of symptoms in the clinical domain and improvement in the psychosocial domain. All psychotherapies will increase BDNF at 6 months of follow-up. As secondary hypotheses, the mechanisms of improvement will be mediated by the therapeutic alliance, motivational status, and defense mechanisms (for PDT). The confounders of this therapeutic improvement will be number of sessions, comorbidities, and medication use. The moderating factors will be gender, age, personality traits, religiosity, and defense mechanisms (for CBT).

## Methods

### Design

The Longitudinal Investigation of Psychotherapy Outcome (LIPO) study will compare three modalities of psychotherapy (PDT, CBT, and IPT) in a longitudinal course, in a naturalistic setting. The choice of the three modalities of psychotherapy is evidence-based and listed in guidelines for indication of first-line treatment for depression (30, 31).

The evaluations will take place in three moments: in the baseline (until the fourth session of psychotherapy) and 6 and 12 months after entering the study. The invited participants will be the patients who are undergoing any psychotherapy in the outpatient clinic of the Hospital de Clínicas of Porto Alegre (HCPA).

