### Participants

All patients included at the HCPA psychotherapy clinic will be evaluated by a fourth-year psychiatry resident with training in psychotherapy. Patients will be referred from the outpatient clinic of clinical psychiatry, pain medicine, or preoperative bariatric surgery. Each patient who agrees will undergo up to five evaluation interviews and engage in discussions with a supervisor. They will be next referred, based on clinical judgment, to the most suitable modality of psychotherapy. The clinic offers three methods of individual psychotherapy: PDP, IPT, and CBT.

The psychotherapy modality will be indicated by general criteria (17), considering the following characteristics: previous favorable experience with some kind of psychotherapy, psychological-mindedness, presence of personality disorder or traits, number of diagnoses of psychiatric disorders, and relief of symptoms. When diagnosed with personality disorder associated with one or more major psychiatric disorders and psychological-mindedness, PDT will be indicated. When there are up to two major psychiatric diagnoses without personality disorder, it will be directed to CBT as well as in the exclusive quest for symptom relief. When the focus of the problem is exclusively up to two of the following: 1) dispute, 2) roles dispute, 3) role transition, or 4) interpersonal deficits and no personality disorder, IPT will be indicated.

Psychotherapeutic care will be provided by psychiatry residents in their second, third, and fourth years of residency in psychiatry under weekly supervision of dialogued interviews. The residents have weekly theoretical seminars related to each of the psychotherapeutic techniques offered throughout the period of residence. They also engage in weekly clinical seminars in which patients are interviewed by teachers to prompt discussions about the clinical aspects related to cases. When there is doubt about patient management, the patient is interviewed by the supervisor.

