2.1 Clinical domain			
Diagnosis (review of medical records)	X		
Psychodynamic Diagnosis (OPD-II)	X	X	
			
Comorbidities	X		
Pharmacological treatment	X	X	X
Personality traits (PID-V)	X		X
Number of sessions		X	X
Type of psychotherapy	X		

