#### Sample Size Estimation

Our sample size calculation relied on the study of Schaf (51) using BDNF serum levels before and after psychotherapy as outcomes. We arrived at a number of 42 subjects for each psychotherapy and control group, considering a significance level of 5% and a power of 80% difference to be detected 0.22 with a standard deviation of 0.43 and losses of 20–30%. We estimated a total sample size of 126 patients and 42 blood donor healthy controls for biological variable (as comparative of BDNF samples). The inclusion criteria will include having started psychotherapy within 1 month, an age above 18 years, and a BDI score greater than 15. The exclusion criteria will include psychotic disorders, current use of psychoactive substances, cognitive deficits, and dementias.

The study will include a subsample of healthy controls for control of blood samples that were recruited from the HCPA blood bank. The exclusion criteria for the control group included conditions (current or past) that precluded participation in the study (e.g., psychiatric disorders and/or psychiatric treatments), immune disorders, use of immunosuppressants, anti-inflammatory drugs used for fewer than 3 weeks, smoking, abuse and/or drug addiction, and infectious diseases for fewer than 3 weeks.

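### Baseline may fall as late as session four, in patients selected on a high BDI and with no untreated patients followed, so the pre-post change cannot bear the causal wording of the main hypothesis

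*Protocol article*

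**What the plan says.** - **Timing (Design).** Assessments are made "in the baseline (until the fourth session of psychotherapy) and 6 and 12 months after entering the study". The section adds: "The invited participants will be the patients who are undergoing any psychotherapy in the outpatient clinic".
- **Entry (Sample Size Estimation).** "The inclusion criteria will include having started psychotherapy within 1 month, an age above 18 years, and a BDI score greater than 15". Table 1 lists BDI among the primary clinical outcomes at baseline, 6 and 12 months.
- **Comparators.** Every patient receives one of the three therapies. The only other group is 42 healthy blood donors, used for BDNF alone and free of psychiatric disorder and treatment (Abstract; Sample Size Estimation).
- **Hypothesis (Aims).** "all three modalities of therapy will produce reduction of symptoms in the clinical domain", and all are expected to raise BDNF by 6 months. The Abstract has a similar sentence.
- **Exposure (Table 1, clinical domain).** "Number of sessions" is marked at 6 and 12 months but not at baseline. Aims and the section on confusion, mediator and moderator factors name it as a confounder.
- **Limitations (Discussion).** These cover therapist heterogeneity, the effect of research interviews, uncontrolled differences between groups, and losses. Regression to the mean, natural course and a baseline taken after therapy has begun are not among them. The BDI threshold appears there only as a way to make the sample more homogeneous.

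**The concern.** The main hypothesis is about improvement within each therapy, so it will be judged on change from baseline. Three things other than the therapy effect enter that change.

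1. **Natural course.** Patients come to treatment when unwell, and some improve with time whatever is done. Without untreated patients this cannot be told apart from a therapy effect. Healthy donors do not show how untreated patients would fare.
2. **Regression to the mean.** Selecting on a high BDI means that some scores are high by chance and fall on retest. This acts directly on BDI and only through correlation on SCL-90-R, BAI, the psychosocial scales and BDNF.
3. **A baseline after the start of therapy.** Change in the first sessions may already be in the baseline value, to a degree that can differ between patients and between modalities.

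The first two inflate apparent improvement, and the third may reduce it. At stake is a significant pre-post decrease being reported as produced by therapy when the design cannot show that.

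**Working it through.** **Step 1: is the study sized on pre-post change?**
Inputs from Sample Size Estimation: difference 0.22, SD 0.43, 5% significance, 80% power, losses 20–30%, 42 per group, with BDNF before and after psychotherapy as the outcome. Statistical Analysis gives two-tailed testing.

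- Paired comparison, normal approximation: n = (SD × (1.960 + 0.842) / difference)² = (0.43 × 2.802 / 0.22)² = 29.98, so 30. With losses: 30/0.75 = 40; 30/0.70 = 42.9, so 43.
- Paired t test, exact: n = 32 gives 80.05% power. With 25% losses: 32/0.75 = 42.7, so 43.
- Two independent groups: 2 × 29.98 = 59.97, so 60 per group; with 20–30% losses, 75 to 86.

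The stated 42 is matched to within two patients by the paired reading and not by the two-group reading. The study therefore appears to be sized on uncontrolled within-group change. This is an inference, because the article does not say whether 0.43 is the SD of change.

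**Step 2: regression to the mean on BDI.**
The documents give only the threshold of 15. Assumed: normal scores, SD 10, mean of the referred population 15 to 25, retest correlation r of 0.6 to 0.8, and the same score used for entry and for baseline.

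Expected fall with no therapy effect = SD × (1 − r) × φ(c)/(1 − Φ(c)), where c = (15 − mean)/SD.

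| Mean | r | c | φ/(1 − Φ) | Fall (BDI points) |
|---|---|---|---|---|
| 15 | 0.6 | 0 | 0.798 | 10 × 0.4 × 0.798 = 3.2 |
| 20 | 0.7 | −0.5 | 0.509 | 10 × 0.3 × 0.509 = 1.5 |
| 25 | 0.8 | −1.0 | 0.288 | 10 × 0.2 × 0.288 = 0.6 |

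**Step 3: what non-therapy change does to a pre-post test.**
Take 34 completers (42 × 0.80 = 33.6) and a two-sided paired t test at 5%. Assume that non-therapy change is 0.2, 0.3 or 0.5 SD of the change score. If therapy does nothing, the test is significant in about 20%, 40% or 81% of studies.

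**Step 4: what a late baseline could cost.**
Assume that 10%, 20% or 30% of the BDNF change precedes baseline and is not made up later. With 32 completers and SD 0.43:

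| Share before baseline | Remaining difference | Power |
|---|---|---|
| 0% | 0.220 | 80% |
| 10% | 0.198 | 71% |
| 20% | 0.176 | 61% |
| 30% | 0.154 | 50% |

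Steps 2 and 3 push towards apparent improvement and step 4 away from it. Nothing scheduled in Table 1 separates them.

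**The case against.** **The clock starts at study entry.** Follow-up is counted from entry and not from session 1, so a patient enrolled at session four still has a full six months between measurements. If change is steady, nothing is lost. The Discussion suggests that BDNF may change more slowly than studies of under 12 weeks can detect, which argues against front-loading. This stands: the power losses in step 4 illustrate one condition and are not an estimate.

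**Eligibility may be judged earlier.** In Procedure, patients who meet the criteria are telephoned and only then attend for consent, blood and questionnaires. The qualifying BDI could thus be a different score from the baseline BDI, and much of the regression would then occur before baseline. A reader might infer from the single baseline entry in Table 1 that one score serves both purposes, but the documents do not establish that. The figures in step 2 hold only if it does.

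**Exposure may be recoverable.** The window is defined by session number, the start date must be known for eligibility, and nothing says that later session counts leave out sessions before baseline. A reader might conclude that early exposure is lost altogether. The documents show only that it is not scheduled as a baseline item.

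**The study is openly naturalistic.** The primary aim speaks of outcomes associated with therapy, and the Introduction concedes a lower level of evidence than randomized trials. That answers any complaint about the missing control arm. It does not answer the causal wording of the hypothesis in the same section, nor the absence of these particular limits from a Discussion that does list others.

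**Conclusion.** The point holds as a mismatch between design and claim. Baseline is taken in patients already in therapy, who were selected on one of the primary outcomes, and no untreated patients are followed. Pre-post change can describe what happens during therapy; it cannot show that therapy produced it. The net direction of bias is unknown.

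The documents do not fix its size. The 0.6 to 3.2 BDI points rest on an assumed mean, SD and retest correlation and on one score serving both purposes. The fall in power from 80% to 71%, 61% or 50% needs 10–30% of the BDNF change to come before baseline, and the paired reading of 0.43. A reader should not infer that the study is underpowered on this account, or that its BDI result is biased by any of these amounts. The change should be made before analysis, but the study need not be redesigned.

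**What to change.** 1. Reword the main hypothesis in Aims and its counterpart in the Abstract as change during therapy. Add regression to the mean, natural course and a baseline after the start of therapy to the limitations, as limits on the conclusion.
2. Record sessions attended and days in therapy at the baseline visit, and include the session count in the GEE model.
3. State which BDI decides eligibility. If it is not already separate from the baseline-visit BDI, use the screening score for eligibility only and the baseline-visit score for analysis.

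The cost is one or two data fields, possibly one more self-report, and a more modest claim.

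Optional: take questionnaires and blood before session 1 where feasible. Participants describes a possible window: "Each patient who agrees will undergo up to five evaluation interviews and engage in discussions with a supervisor". This is a trade-off, because modality is assigned only after those interviews. It would mean enrolling patients not yet assigned, some of whom may never start, and the alliance scale would still need a therapy session to refer to. None of these steps supplies an untreated comparison, so the rewording is needed in any case.

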### Participants

All patients included at the HCPA psychotherapy clinic will be evaluated by a fourth-year psychiatry resident with training in psychotherapy. Patients will be referred from the outpatient clinic of clinical psychiatry, pain medicine, or preoperative bariatric surgery. Each patient who agrees will undergo up to five evaluation interviews and engage in discussions with a supervisor. They will be next referred, based on clinical judgment, to the most suitable modality of psychotherapy. The clinic offers three methods of individual psychotherapy: PDP, IPT, and CBT.

The psychotherapy modality will be indicated by general criteria (17), considering the following characteristics: previous favorable experience with some kind of psychotherapy, psychological-mindedness, presence of personality disorder or traits, number of diagnoses of psychiatric disorders, and relief of symptoms. When diagnosed with personality disorder associated with one or more major psychiatric disorders and psychological-mindedness, PDT will be indicated. When there are up to two major psychiatric diagnoses without personality disorder, it will be directed to CBT as well as in the exclusive quest for symptom relief. When the focus of the problem is exclusively up to two of the following: 1) dispute, 2) roles dispute, 3) role transition, or 4) interpersonal deficits and no personality disorder, IPT will be indicated.

Psychotherapeutic care will be provided by psychiatry residents in their second, third, and fourth years of residency in psychiatry under weekly supervision of dialogued interviews. The residents have weekly theoretical seminars related to each of the psychotherapeutic techniques offered throughout the period of residence. They also engage in weekly clinical seminars in which patients are interviewed by teachers to prompt discussions about the clinical aspects related to cases. When there is doubt about patient management, the patient is interviewed by the supervisor.

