#### Confusion/Mediator/Moderator Factors

The mediating factors will be therapeutic alliance, motivation, and defense mechanisms (for PDT only). The moderating factors will be gender, age, religiosity, stressors, social support, personality traits, and defense mechanisms (for CBT and IPT). The confounding factors considered will be diagnosis, medication use, number of sessions, and comorbidities.

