#### Statistical Analysis

Shapiro–Wilk test will be used to determine normality. For parametric distributions, dependent or independent *t* tests will be performed. To determine differences between categorical variables, the chi-squared test will be used. For nonparametric distributions, we will use the Wilcoxon test and Mann–Whitney *U* test to compare nonrelated and related means, respectively. A generalized estimating equations (GEE) model will be used to investigate multivariate repeated measurements. The Hayes method will be used to analyze the mediators (52), and the multivariate regression will be used to analyze the confounders. *Post hoc* analyses will be performed using the Bonferroni test.

The data will be expressed as mean ± standard deviation (SD), and a *p* value less than or equal to 0.05 will be considered to be statistically significant (two-tailed). The statistical analyses will be performed using the SPSS version 20.0 software package (IBM^®^, New York, USA).

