Limitations of this study include the heterogeneity of the training and experience of the resident psychiatrists and the absence of evaluation from their point of view in the psychotherapeutic process. As a study is naturalistic, there is no way to control the impact of the researchers’ interviews. We will collect a series of demographic data, use of medications, and number of sessions to control possible confounders, but we know that because it is an open study, there is no way to control all differences between groups. Also, psychotherapy studies often have large amounts of losses (16). To control this bias, we will compare the clinical and demographic characteristics of the lost sample with those that continue in relation to the baseline. As for the multiplicity of diagnoses that may be found, to homogenize the sample, we will consider for inclusion the BDI value >15.

Studies such as this one seek to contribute to the foundations of public health policies and investments for the treatment of patients with severe mental illnesses who are at risk of hospitalization and suicide. These types of investigations also seek to promote mental health, rehabilitation, and social reintegration. Understanding the mediating and biological mechanisms of the psychotherapeutic process can help to optimize these interventions and facilitate their indication according to the psychopathological profile and the severity of the patients.

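### The stated confounder list does not match the criteria that assign modality and is not tied to the GEE, so the modality contrast may reflect case mix

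*Protocol article*

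**What the plan says.** **Assignment.** The Participants section of the protocol article refers patients by clinical judgment, using general criteria: "previous favorable experience with some kind of psychotherapy, psychological-mindedness, presence of personality disorder or traits, number of diagnoses of psychiatric disorders, and relief of symptoms". More specific rules follow. For PDT: "When diagnosed with personality disorder associated with one or more major psychiatric disorders and psychological-mindedness, PDT will be indicated". For CBT: "When there are up to two major psychiatric diagnoses without personality disorder, it will be directed to CBT", with a second route for patients who seek only symptom relief. For IPT, the problem must lie in one or two interpersonal areas: "interpersonal deficits and no personality disorder, IPT will be indicated".

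**Confounders.** Under Confusion/Mediator/Moderator Factors: "The confounding factors considered will be diagnosis, medication use, number of sessions, and comorbidities". The same paragraph makes personality traits a moderator. The hypotheses in Aims give a shorter list, without diagnosis. The Abstract and the secondary aim give longer lists that do not separate confounders from mediators; these include personality traits and previous psychotherapeutic treatment. The limitations paragraph of the Discussion says: "We will collect a series of demographic data, use of medications, and number of sessions to control possible confounders".

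**Analysis.** The Abstract states: "The comparison between the modalities of psychotherapy will be by generalized estimating equations (GEE) model". It gives confounders to a multivariate logistic regression. The Statistical Analysis section says "A generalized estimating equations (GEE) model will be used to investigate multivariate repeated measurements" and gives confounders to a multivariate regression. Neither names covariates for the GEE.

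**The concern.** A variable that decides which therapy a patient receives, and that also bears on outcome, confounds the comparison of therapies. Here the protocol writes those variables down in its assignment rules, but the confounder list a few sections later is largely a different set. An analyst who followed that list would control for number of sessions, which is partly a consequence of the therapy received, and might not control for personality disorder, the characteristic that most sharply separates PDT from the other two.

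The Design section and the Abstract both present the study as a comparison of three modalities, and the Discussion hopes to inform public health policy. A difference between PDT and CBT/IPT could be read as an effect of the therapy when it is wholly or partly a difference between the patients sent to each.

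**Working it through.** **1. Assignment criteria against the confounder lists**

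| Criterion in Participants | Confusion/Mediator/Moderator Factors | Aims, hypotheses | Joint lists (Abstract, secondary aim) | Table 1, baseline |
|---|---|---|---|---|
| Personality disorder | Not named; may fall under diagnosis or comorbidities | Not named; may fall under comorbidities | Not named as such; traits are | Diagnosis by record review; PID |
| Personality traits | Moderator only | Moderator only | Listed | PID |
| Psychological-mindedness | Absent | Absent | Absent | No named measure |
| Number of diagnoses | Partly, via diagnosis and comorbidities | Partly, via comorbidities | Partly, via both | Both recorded |
| Previous favorable psychotherapy | Absent | Absent | History of previous treatment listed | No row visible |
| Wish for symptom relief (goal) | Absent | Absent | Absent | No row visible |

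Two further observations:
- Number of sessions is in every list. Table 1 records it only at 6 and 12 months, so it cannot be a baseline confounder of modality.
- The joint lists cannot serve as an adjustment set. They contain type of psychotherapy, which is the exposure, and therapeutic alliance, which the protocol itself names as a mediator.

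**2. Can the sample-size effect serve as a yardstick?**

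Inputs from Sample Size Estimation: difference 0.22, SD 0.43, two-sided 5%, power 80%, losses 20–30%, 42 per group.
- Before-after change: n = (0.43 × 2.80 / 0.22)² = 29.98, so 30. With losses, 30/0.8 gives 38 and 30/0.7 gives 43. The stated 42 lies in this range.
- Two independent groups: 2 × 29.98 gives 60 per group, or 75 to 86 with losses. This does not give 42.

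So 0.22/0.43 = 0.51 SD is a within-group change in BDNF, not a planned difference between modalities. It is not used below.

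**3. Possible size of the case-mix difference**

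The documents give neither the personality-disorder share by modality nor its prognostic effect. Both are assumed.

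Bias (SD) = difference in share × prognostic effect (SD)
- Low end: 0.5 × 0.2 = 0.10 SD
- High end: 1.0 × 0.5 = 0.50 SD

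Chance of a false two-sided 5% finding, without adjustment, for one pair of modalities and one outcome, with SE = √(2/n):

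| Bias | 42 per arm (SE 0.218) | 29 per arm (30% loss, SE 0.263) |
|---|---|---|
| 0.10 SD | 7% | 7% |
| 0.50 SD | 63% | 48% |

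**4. What adjustment for personality disorder would cost**

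For two equal arms with shares p₁ and p₂ and mean share p̄:

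R² = [(p₁ − p₂)²/4] / [p̄(1 − p̄)], variance inflation = 1/(1 − R²)

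| Assumed shares | R² | Variance inflation | Information left in 42 per arm |
|---|---|---|---|
| 0.7 vs 0.2 | 0.25 | 1.3 | about 31 |
| 0.9 vs 0.1 | 0.64 | 2.8 | about 15 |
| 0.95 vs 0.05 | 0.81 | 5.3 | about 8 |
| 1.0 vs 0 | 1 | not estimable | none |

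Adjustment is workable if the rules are applied loosely and fails if they are applied without exception. The actual overlap therefore has to be shown.

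**The case against.** The strongest reply is that this is a condensed article, and GEE covariates are commonly left to the full protocol or analysis plan. That stands as far as it goes. A reader might infer that the modality comparison is unadjusted, but the text never says so, and the Discussion states an intention to control confounders. What is not merely left out is the confounder list: it is stated, in versions that disagree with each other and with the assignment rules.

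It can also be said that the list does not miss everything. This stands too. A reader might infer that every assignment variable is omitted, but diagnosis and comorbidities cover number of diagnoses at least in part and may take in personality disorder, and the joint lists name personality traits and previous psychotherapy. Calling traits a moderator does not bar adjustment either, since a moderation model normally carries the main effect. Psychological-mindedness and treatment goal are in no list.

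A third inference is that personality disorder separates PDT from CBT/IPT completely, so that no adjustment could help. The documents do not support that. The criteria are general and applied by judgment, the PDT rule does not say that only such patients receive PDT, and CBT has its symptom-relief route. Overlap is unknown.

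Finally, the main hypothesis is improvement in all three modalities, no superiority hypothesis is stated, and the Discussion concedes that not all group differences can be controlled. These points limit the consequence. They do not remove the stated comparison, and a general concession does not tell the reader that the assignment rules themselves may leave little overlap on one variable.

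**Conclusion.** The point holds as an inconsistency between how patients are assigned and what the protocol says it will control. The main confounder list does not name personality disorder, psychological-mindedness, previous psychotherapy or treatment goal. It includes a post-assignment variable, conflicts with the other lists, and is not attached to the GEE.

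The modality contrast, chiefly PDT versus CBT/IPT, may therefore reflect case mix. Direction and size are unknown. The range of 0.10 to 0.50 SD, and the false-positive chance of 7% to 63% at 42 per arm, rest wholly on the assumed share difference and prognostic effect, and on no adjustment being made. It would be tempting to express this bias as a fraction of the 0.51 SD in the sample-size calculation. That would be wrong, because the 0.51 SD is a before-after BDNF change. The hypothesis of improvement within each modality is not distorted in the same way.

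**What to change.** In Confusion/Mediator/Moderator Factors and in Statistical Analysis:

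1. State one baseline adjustment set matched to the criteria in Participants, and say that it enters the GEE modality comparison: baseline value of the outcome, personality disorder or baseline PID-5, number of diagnoses and previous psychotherapy, plus psychological-mindedness and treatment goal if recorded at referral.
2. Bring the lists in the Abstract and Aims into line with it.
3. Do not treat number of sessions as a baseline confounder.
4. Report the distribution and overlap of these variables by modality.
5. Label PDT versus CBT/IPT as descriptive where overlap is inadequate.

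None of this alters how patients are referred. Most of the data are already planned. Psychological-mindedness and treatment goal would need a couple of items on the referral form, best added early because they may not be recoverable later. The price is a less precise adjusted contrast (variance inflation of about 1.3 to 5.3 under the assumed shares) and a narrower claim for PDT. With about 42 patients per arm and 20–30% losses, the covariate set should stay short.
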